## Methods

### Study design and process

The IDDEAS project is an experimental, mixed-methods evaluation study, within CAMHS in Norway. The study evaluates the IDDEAS CDSS model (see Fig. 1) for diagnosis and treatment in CAMHS in Norway; IDDEAS will use ADHD as the first clinical model paradigm. The study consists of the following four stages:

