##### Phase 1: vignette-based evaluation

After completion of informed consent procedures, including assessments of conflicts of interest, clinicians will be asked to complete a brief demographic questionnaire. They will then be provided the educational manual on how to navigate the IDDEAS system. Clinicians will then be asked to critically appraise ten previously validated clinical case vignettes (i.e., fictional patient cases that have been “referred” for assessment of ADHD). Clinicians will first appraise five of the cases without the use of the system and five using the CDSS. The cases will be randomly allocated by the PhD student with the project and verified by the project leader. The allocation sequence will be computer generated.

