##### Phase 2: live patient evaluation

Phase 2 will entail a live patient evaluation study of the IDDEAS CDSS model for the diagnosis and treatment of ADHD among children and adolescents in which seven standardized patient-encounter videos will be assessed with and without the use of the IDDEAS system. The aim of this phase of the study is to determine whether IDDEAS in its entirety can: meet the desired requirements; can yield an output that meets specifications with acceptable capability.

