##### Quantitative methods

The Likert scale items will be assessed based on inter-rater reliability in accordance with pre-specified and previously validated criteria. The usability, content validity, and user engagement data will be compiled and analyzed with statistical analysis software (SPSS software platform) to determine whether the criteria are met for each measurement (i.e., SUS ≥ 70; UES ≥ 70; CVI > 0.80) [38]. The criteria will be analyzed by computing the average of the rating scores proposed by participants for each Likert item and finding the degree of inter-rater agreement on the IDDEAS system attributes (i.e., prompt/alert provided in system user-interface).

The sensitivity, specificity, and relevance of the IDDEAS system for ADHD diagnosis and treatment will also be assessed based on overall percentage of agreement among participants on appropriate diagnosis, as well as the proposed biopsychosocial treatment plan. A mixed model logistic regression will be used with correct diagnosis as the dependent variable, decision support (yes or no) and patient status (ADHD or non-ADHD) as fixed effects.

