#### Outcomes

The primary outcome of the study will be the clinical utility of the IDDEAS CDSS for diagnosis and treatment of child and adolescent mental health disorders. The primary outcome will be measured by reviewing participants’ clinical diagnosis and treatment plans as a measure of sensitivity and specificity when using the CDSS compared to when not using the CDSS, upon completion of both phases of the evaluation.

The secondary outcomes of the study will be subjective measures. The three secondary outcome measures are perceived clinical usability, perceived clinical relevance and validity, as well as perceived appropriateness of the IDDEAS CDSS. The perceived clinical usability of the CDSS will be measured using the system usability scale (SUS) [33, 39, 40]. The perceived appropriateness of the CDSS will be measured using the user-engagement scale (UES) [41–43]. The perceived clinical relevance and validity of the system’s user-interface will be measured using the content validity index (CVI) [44].

All outcomes will be measured directly following both phases of the evaluation of the IDDEAS CDSS (i.e., within 24 h).

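### The primary outcome attaches sensitivity and specificity to treatment plans, for which the article states no correct/incorrect status, and is worded wider than the ADHD evaluation that will be run

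*Protocol article*

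**What the plan says.** The Outcomes section of the protocol article names one primary outcome, the "clinical utility of the IDDEAS CDSS for diagnosis and treatment of child and adolescent mental health disorders". It is to be measured from participants' "clinical diagnosis and treatment plans as a measure of sensitivity and specificity when using the CDSS", compared with not using it, after both evaluation phases.

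The Quantitative methods part of Data analysis gives two ways of handling this. Sensitivity, specificity and relevance, there tied to ADHD, are assessed on "overall percentage of agreement among participants on appropriate diagnosis, as well as the proposed biopsychosocial treatment plan". A mixed logistic regression is then specified with "correct diagnosis as the dependent variable, decision support (yes or no) and patient status (ADHD or non-ADHD) as fixed effects".

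On scope, Study design and process states that "IDDEAS will use ADHD as the first clinical model paradigm", and the abstract limits the evaluation to ADHD. The ten Phase 1 vignettes are "fictional patient cases that have been “referred” for assessment of ADHD". Phase 2 concerns "diagnosis and treatment of ADHD among children and adolescents in which seven standardized patient-encounter videos will be assessed" with and without the system.

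**The concern.** Sensitivity is the proportion of truly positive cases called positive, and specificity the proportion of truly negative cases called negative. Both need a binary call and a binary truth for each case. An ADHD diagnosis has both in this design. For a treatment plan the article does not say what counts as positive, negative, correct or incorrect, yet the primary outcome places plans and diagnoses under the same two statistics.

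The outcome is also worded for the mental health of children and adolescents at large, while the case material and the analysis text concern ADHD.

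Two things are at stake. A positive diagnostic result for ADHD would satisfy the primary outcome as worded, although treatment had not been tested for correctness and other referral questions had not been tested at all. And if a rule for judging plans is first devised once plans have been read, the data can shape it.

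**Working it through.** No figure in the plan needs correcting here. The check sets the primary outcome beside each part of the article that should support it.

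**1. Truth status.** The only case-level truth stated is patient status, ADHD or non-ADHD, in the regression.
- Diagnosis: P(correct | ADHD) is sensitivity and P(correct | non-ADHD) is specificity, so both are defined with and without IDDEAS.
- Treatment plan: no call and no truth are stated. The validation of vignettes in Stage 1 asks whether they are credible representations of patients. It does not set a reference plan.

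**2. The stated method for plans.** Agreement among participants compares readers with each other, not with a reference. Take 30 clinicians who all write the same inadequate plan for a case:
- agreement = 30/30 = 100%
- plans that are appropriate = 0/30 = 0%

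The method can therefore return its best value when correctness is at its worst. It cannot yield the measure named under Outcomes.

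**3. The inferential model.** The dependent variable is correct diagnosis. No model has a plan-based outcome.

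**4. The sample size.** The Sample size section assumes specificity rising from 0.50 to 0.80, p < 0.05, 80% power, and states 30. The article does not give the formula or the sidedness. With two independent proportions and a pooled normal approximation:

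n per condition = [z_α √(2 p̄ (1 − p̄)) + z_β √(p₁(1 − p₁) + p₂(1 − p₂))]² / (p₂ − p₁)²

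Here p̄ = 0.65, so √(2 × 0.65 × 0.35) = 0.6745 and √(0.25 + 0.16) = 0.6403.
- One-sided: (1.645 × 0.6745 + 0.842 × 0.6403)² / 0.09 = 30.2, rounded up to 31. The arcsine version gives 29.9.
- Two-sided: (1.960 × 0.6745 + 0.842 × 0.6403)² / 0.09 = 38.5, rounded up to 39.

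The figure of 30 is close to the one-sided result. Whichever variant was used, the rates entered are specificities, and only the diagnosis has a specificity defined in this article. Nothing in the calculation concerns plans.

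**5. Scope.**

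| Place in the article | Scope |
|---|---|
| Outcomes; first project objective; opening of the Discussion | Child and adolescent mental health in general |
| Abstract, Methods/design | ADHD |
| Study design and process | ADHD as the first model condition |
| Phase 1 | 10 vignettes, all referred for ADHD assessment |
| Phase 2 | 7 videos, in a phase on ADHD |
| Data analysis, Quantitative methods | ADHD |

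Of 10 + 7 = 17 cases, none is described as arising from another referral question. The outcome is wider than every operational section.

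**The case against.** The strongest reply is that this is a condensed article. Rules for scoring plans commonly sit in a full protocol or analysis plan, and the article does say that data go onto standardized score sheets. Treatment is also not left out of the analysis, since agreement on plans is specified. The ADHD limit is disclosed in several places, including the sentence on sensitivity and specificity, so a fair reader would not be misled about scope.

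Part of this stands. The absence of scoring detail alone would be no finding, and the scope problem is one of inconsistent wording, not a concealed claim. What does not fall away is that the article states a measure for plans in one section and a method in another that cannot produce it. A missing annex does not explain that.

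Several stronger readings are tempting and should be resisted:
- **Only ADHD cases are read, so specificity cannot be estimated.** A referral for ADHD assessment is a question, not a diagnosis, and the regression includes non-ADHD status. Non-ADHD cases are foreseen.
- **The outcome claims utility for all disorders.** The text is general in wording but does not say all.
- **A plan can never be a true positive or true negative.** A plan could be judged against an expert reference. The accurate statement is that this article defines none.
- **Plans will be judged by people who know whether the system was used.** The article does not say who judges plans or what they can see, so observer bias would be conjecture.

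**Conclusion.** The point holds for the treatment half of the primary outcome and for the scope of its wording. One of two named components, the treatment plan, has no stated correct/incorrect status, no model and no part in the sample size. Its stated method, agreement among participants, does not measure correctness. The outcome also extends beyond the ADHD setting from which all 17 cases come.

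It would go too far to infer that the primary outcome as a whole cannot be answered. The comparison of ADHD/non-ADHD diagnosis with and without IDDEAS has a defined truth and a stated model, and it survives intact.

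The conclusion rests on the article alone and assumes that no fuller document gives plans a reference standard. If one does, the treatment measure may be sound, but the agreement sentence in Data analysis and the scope in Outcomes would still need to be brought into line. It also assumes that the model will be used to read the effect of decision support among ADHD and among non-ADHD cases, which is what sensitivity and specificity require.

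**What to change.** 1. Restate the primary outcome as sensitivity and specificity of the participant's ADHD/non-ADHD diagnosis with versus without IDDEAS, analysed by the mixed logistic regression already specified.
2. Limit the primary conclusion to diagnosis in cases referred for ADHD assessment, and align the Outcomes wording with the abstract, Study design and process, and Data analysis.
3. Make treatment-plan appropriateness a separate secondary outcome. Score each plan against reference elements that the Consortium fixes for each case before any plan is read, in place of agreement among participants.
4. Cover the seven videos as well as the ten vignettes. The article describes Consortium validation for the vignettes only, and the outcome spans both phases.

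The cost is a narrower headline claim and a short reference list for each of 17 cases. No additional participants or cases are needed. The vignette lists can be drawn up in the validation meetings already planned, whose clinicians are excluded from the evaluation. The video lists need a comparable step.

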### Stage 4: Implementation & Dissemination

From the outset of the IDDEAS project, a scientific communication and dissemination plan will be implemented in line with both the Golden Road and the Green Road for dissemination. Findings and relevant study information will be regularly disseminated to the academic community, healthcare professionals, service-user organizations and the general public at conferences, congresses, workshops, and through social-media platforms (i.e., Twitter, Facebook, Instagram, etc.). Scientific communication will be disseminated as peer-reviewed publications in both national and international journals annually. Practical information on the IDDEAS CDSS will also be made available for all end-users, including an informative website, online tutorial and user guides. Prior to implementation of IDDEAS, preselected Consortium members and clinical experts will guide trial participants through training courses in order to qualify the clinicians as trainers for future IDDEAS End-User training courses. Follow-Up reviews and support meetings will be held to receive the clinicians’ feedback on using the IDDEAS CDSS. IDDEAS CDSS workshops will be held at the Norwegian CAMHS annual congress (i.e., N-BUP Kongressen).

## Discussion

IDDEAS will utilize qualitative and quantitative methods to determine whether the implementation of a clinical guideline and data-driven CDSS model in CAMHS will improve the quality of diagnoses and treatment of child and adolescent mental health disorders. The inclusion of two phases of evaluation within the IDDEAS trial will allow for a thorough assessment of the specific aspects of the CDSS that are suitable and those that need to be addressed for improvement of clinical care based on clinician’s subjective perception, as well as objective statistical analysis.

IDDEAS’ expected impacts include, but are not limited to, improved use of available health data, integration of predictive interventions in care, better management of complex clinical situations in child and adolescent mental health, enhanced collaboration among stakeholders involved in patient care, and amplified inter-service coordination in management of patient’s health. Furthermore, IDDEAS will help to improve patients’ understanding of the clinical decision- making involved in their treatment, as well as help ensure greater participation and improved transparency for the patients’ families. Overall IDDEAS will improve the quality of mental health care for children and adolescents by using innovative data-analytics within the CDSS model to provide support to clinicians that is evidence-based and customized to meet the needs of each individual patient. With quality improvement of clinical standards and enhanced precision of care, IDDEAS will also improve the efficiency of practices, allowing for more patients to be seen and receive a diagnosis in a timely-manner.

Our research will provide a comprehensive understanding of how to approach the use of a CDSS as a novel innovation for CAMHS. All limitations and challenges faced through the processes of designing, modelling, evaluating and testing the implemented IDDEAS CDSS model, can serve as valuable learning opportunities for future CDSS implementations in CAMHS.

## Data Availability

The datasets used and/or analyzed during the current study are available from the corresponding author on reasonable request.

## Abbreviations

ADHD: Attention-deficit/hyperactivity disorder
ASD: Autism spectrum disorder
BUP: Barne-og ungdompsykiatrisk poliklinikk/child and adolescent psychiatric clinic
CAMHS: Child and adolescent mental health services
CCQ: Clinical competence question
CDSS: Clinical decision support system
CDS: Clinical decision support
CVI: Content validity index
DBD: Disruptive behavioural disorders
DPIA: Data protection impact assessment
EHR: Electronic health record
ICT: Information and communication technologies
IDDEAS: Individualized digital decision assist system
NFR: Norsk forskningsrådet/Norwegian research council
OWL: Web ontology language
PCP: Primary care provider
PID: Personal identifiers
RCT: Randomized controlled trial
SUS: System usability scale
UES: User-engagement scale
WHO: World health organization
YLD: Years lived with disability
